### **3.6 Exploratory Analyses**

Further analyses focusing on the total effectiveness of Rotarix include the following:

- a. Total effect analyses of rotavirus diarrhea, but adjusting for all relevant covariates ( $p < 0.1$  and  $[RR > 1.5 \text{ or } RR < 0.67]$ , in a forward stepwise model).
- b. Total effect analyses of rotavirus diarrhea, but using a Cox survival model as in the indirect analyses above, but with a focus on covariates of interest. In particular, two time-varying dummy covariates will be used to track the three seasons: March through May; June through October; November through February. Two interaction terms for Rotarix \* season will be added to look at variable effectiveness. (Note: although Bangladesh is land of the *Sadartu*, five dummy variables for these six seasons would be unwieldy).

In addition, we will look for variable effectiveness by gender and SES quintile.

Finally, a 'check' analysis will be performed in the Overall population to compare rates of non-rotavirus diarrhea between study areas. Unless there are non-specific effects of Rotarix on these kinds of cases, we would expect the rates to be very similar.

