## **1 INTRODUCTION**

The main purpose of this document is to describe the planned statistical analyses of this study so as to avoid “data dredging” at the time of preparing analyses to inform policy and for publication. Some background information and sample size calculations are copied here from the protocol dated 21.02.11 for ease of reference.

This document will guide analyses and may be given to journal editors for clarification of analyses and their timing. This document is being finalized months before the end of data collection, without any knowledge of treatment arm-specific results, and only a general idea of enrollment and total numbers of events.

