### *Secondary Aims*

*1. To evaluate the total effectiveness of Rotarix in reducing rates of acute diarrhoea due to rotavirus, as detected by patients admitted to a study treatment facility, among vaccinated infants and young children from villages where Rotarix is introduced compared to unvaccinated infants and young children from villages where Rotarix is not introduced.*

Main analysis, “overall effectiveness” primary analysis population: with the modification of starting observation time at 12 weeks instead of 6 weeks of age. A Poisson regression with Pearson scale parameter (calculated at the village level) will be fit, offset with person-years of exposure, with a dummy covariate for village randomization arm status and a dummy covariate for villages in the Matlab service area.

Additional analyses:

- a. As in 1., but for all (not just first) cases of rotavirus diarrhea.
- b. As in 1. and 1.a, but for the mITT population.

*2. To evaluate the indirect effectiveness of Rotarix in reducing rates of acute diarrhoea due to rotavirus, as detected by patients admitted to a study treatment facility, among unvaccinated*

*infants and young children from villages where Rotarix is introduced compared to those from villages where Rotarix is not introduced.*

*Analyses are given according to the populations a, b, c given above.*

a) Those aged at least 20 weeks as of Nov 1, 2008 (Apr 1, 2009), with censoring at earliest of 2 years of age or Mar 31, 2001, whichever comes first. Also included are those who in-migrate between ages 20 weeks-2 years. Poisson regression as described above will be used; all cases (first and subsequent) will be used.

b) Those in the Overall population, but with censoring at first OPV dose. Because of the high coverage, this will not comprise many person-years. Poisson regression as described above will be used; all cases (first and subsequent) will be used.

c) All person-time contributed by infants or children who were between 6 weeks and 2 years of age at some point during the study period.

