where  $\lambda_0(t)$  is the unspecified baseline hazard function.  $X_i$  does not appear by itself because there is no expected effect of whether a child lives in a Rotarix or control village *per se*, as that was determined through randomization.

The indirect effects at any given level of coverage are estimated by taking the difference of the relevant covariates. For example,  $\exp(\beta_6 - \beta_9)$  gives the relative hazard of those in a highly Rotarix-immunized village compared to those in a highly OPV-only immunized village. Note there will not be a great deal of power for these comparisons, however.

It will also be advisable to add two time-varying dummy variables to track the three main seasons (see the seasonality discussion below).

The best way to analyze these data is to use a gamma frailty model that assigns a random intercept term to each village to account for within-village correlation. Stata has a function for this, although it will take some careful work to split up each child's observation time into a number of intervals to account for all the time-varying covariates. It may also be possible to use the SAS PROC SURVEYPHREG to estimate a robust variance to account for the correlation. The advantage to this approach is that SAS allows for continuously-varying time-varying covariates that are relatively easily coded. If this specification in SAS, that will be the preferred approach for analysis.

*3. To evaluate the direct effectiveness of Rotarix in reducing rates of acute diarrhoea due to rotavirus, as detected by patients admitted to a treatment facility, among vaccinated infants and young children from villages where Rotarix is introduced compared to unvaccinated infants and young children from villages where Rotarix is introduced.*

This direct effect is best estimated by  $\beta_2$  in the above model, which is the remaining effect of Rotarix after accounting for the indirect effects. This will be run for the mITT population.

A second estimate will be provided by applying a Cox model to the Direct effect population (i.e. the mITT population only in Rotarix villages), with a time-varying covariate for receipt of first dose of Rotarix.

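### The exploratory covariate-adjusted total-effectiveness analysis selects covariates by a stepwise rule that usually drops moderate child-level risk factors; a fixed list should replace it (low severity)

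*SAP*

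**What the plan says.** Section 3.6 (Exploratory Analyses) opens with "Further analyses focusing on the total effectiveness of Rotarix include the following". Item a is then "Total effect analyses of rotavirus diarrhea, but adjusting for all relevant covariates", where a covariate counts as relevant if p<0.1 and its RR is above 1.5 or below 0.67, selected "in a forward stepwise model". No candidate list, forced-in terms or coding rule is given.

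The analysis being modified is Secondary Aim 1 in section 3.5: "A Poisson regression with Pearson scale parameter (calculated at the village level) will be fit, offset with person-years of exposure", with fixed terms for arm and service area. Its main version uses the overall-effectiveness primary population with observation from 12 weeks of age. Additional analysis b repeats it in the mITT population. Under the first-priority definition in section 3.2, that population compares Rotarix recipients who had OPV1 in Rotarix villages with OPV1 recipients in non-Rotarix villages.

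Section 3.6 also states that "we will look for variable effectiveness by gender and SES quintile". Section 1 gives the SAP's purpose as "to describe the planned statistical analyses of this study so as to avoid" data dredging.

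**The concern.** A confounder matters through its relation to the outcome and its imbalance between the groups compared. This rule looks only at the first. It also requires the estimated RR to exceed a fixed size, so it treats precisely and imprecisely measured covariates very differently. A child-level factor with a real but moderate RR can be clearly significant and still be refused. For an imprecisely estimated village-level factor, any estimate reaching p<0.1 is already close to or beyond RR 1.5, so the size condition filters little.

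The cut-off also depends on coding. As an illustration (this RR is not in the SAP), suppose SES has an RR of 0.85 per quintile. Entered as a linear term it fails, because 0.85 lies between 0.67 and 1.5. Entered as categories, top versus bottom is 0.85^4 = 0.52, which meets the RR condition. The SAP names quintiles but does not say how a multi-level covariate is judged, so this could be decided after the data are seen.

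At stake is the credibility of the SAP's general covariate-adjusted total-effect estimate, mainly in the mITT population, where acceptance of vaccine enters the definition of one arm only.

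**Working it through.** **Inputs from the SAP.** Section 2.5.1: 268 events, 77 events without clustering, ICC 0.02, mean village size 65, size CV 0.96, design effect (DE) 3.48 with a later range of 2.9-4.5, 50% effectiveness, 3.5% attack rate. Section 2.5 also gives 11,650 expected infants. Section 3.6: p<0.1 and RR >1.5 or <0.67.

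**Step 1: reproduce the plan's figures.**
- DE = 1 + [(0.96² + 1) × 65 − 1] × 0.02 = 3.478.
- 77 events: exact conditional binomial, 1/3 against 1/2, lower tail 0.025, power 82.4%.
- 77 × 3.48 = 267.96, so 268 events.
- 268 / (0.035 × 0.75) = 10,209.5, so 10,210 infants.

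All agree with the SAP.

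**Step 2: entry rule.** For a binary covariate with prevalence q, SE(log RR) ≈ √[DE / (268 × q × (1 − q))]. DE is 1 for a child-level covariate spread evenly within villages and 3.48 for a village-level one. Entry requires |log RR| > max(1.645 × SE, log 1.5), with log 1.5 = 0.405.

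**Step 3: child-level covariates.** At q = 0.5, SE = √(1/67) = 0.122 and 1.645 × SE = 0.201, so the RR cut-off governs. For true RR 1.3 (log 0.262), z = (0.405 − 0.262)/0.122 = 1.17 and entry is 12%. For RR 1.4 (log 0.336), z = 0.56 and entry is 29%.

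| True RR | q | Left out by the rule | Left out by p<0.1 alone |
|---|---|---|---|
| 1.3 | 0.5 | 88% | 31% |
| 1.4 | 0.5 | 71% | 13% |
| 1.3 | 0.2 | 83% | 47% |
| 1.4 | 0.2 | 67% | 29% |

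More events do not help. With all 11,650 infants, 11,650 × 0.035 × 0.75 = 306 events, SE = 2/√306 = 0.114, and entry at q = 0.5 is about 11% and 27%.

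**Step 4: village-level covariates with no effect.** At q = 0.5, SE = √(3.48/67) = 0.228. p<0.1 already needs an RR of about exp(1.645 × 0.228) = 1.46, so the cut-off adds little: z = 0.405/0.228 = 1.78 and chance entry is 7.5%. At q of 0.3 or less the p-value governs and entry is 10%. Over DE 2.9-4.5 the range is 5.1-10%. If ten independent candidates were tried (an assumption; the SAP gives no number), at least one would enter by chance with probability 54-65%.

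**Step 5: size of the bias from one omission.** For an omitted covariate with rate ratio g and prevalences p1 and p0 in the two groups, bias = [1 + p1(g − 1)] / [1 + p0(g − 1)].
- g = 1.3, 55% against 45%: 1.165/1.135 = 1.026.
- g = 1.4, 60% against 40%: 1.24/1.16 = 1.069.

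The imbalances are assumed. A rate ratio of 0.50 would become 0.513 to 0.535, or move as far the other way. For scale, at 268 events split 1:2 the SE of the log rate ratio is √[3.48 × (1/89.3 + 1/178.7)] = 0.24, so the shift is about 0.1 to 0.3 of a standard error.

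**The case against.** The strongest defence is status. Item a is exploratory, no conclusion is tied to it, and the primary and main total-effect models have fixed covariates. That stands and sets the severity.

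Second, the thresholds were written down before arm-specific results were known, so this is a pre-specified algorithm and not data dredging. That stands in part. The thresholds are fixed, but the candidate pool and coding are not, so the outcome data still settle the model.

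Third, the RR condition lowers chance entry: 7.5% is below the 10% that p<0.1 alone allows, and a null child-level covariate at 50% prevalence enters only 0.1% of the time. True, but the price is losing most moderate child-level factors.

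Fourth, the main total-effect analysis follows village assignment regardless of receipt, the mITT definition already requires OPV1 in both arms, and coverage above 90% is expected. This confines the confounding argument to the mITT contrast and makes large imbalance less likely.

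A reader might also infer that adding sex or SES makes the analysis lose its correction for village clustering, because those covariates need child-level or cell-level records. The SAP does not support that. Item a changes only the covariates, so it inherits the Secondary Aim 1 specification: "A Poisson regression with Pearson scale parameter (calculated at the village level) will be fit". The Cox model that item b borrows is to "use a gamma frailty model that assigns a random intercept term to each village to account for within-village correlation", with a robust variance as the alternative. The correction would be lost only if the scale were computed on child records, contrary to the text. What remains is that the SAP does not say how the village-level scale is obtained once child-level covariates are in the model.

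**Conclusion.** The point holds at low severity. The selection rule in section 3.6, item a, is a poor way to choose adjustment covariates: at 268 events it leaves out 71-88% of child-level covariates with true RR 1.3-1.4 at 50% prevalence, admits 7.5-10% of null village-level ones at DE 3.48, ignores imbalance, and depends on an unstated coding. The consequence is probably modest, about 3-7% of the rate ratio for one omitted covariate, and is mainly relevant to the mITT contrast.

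These figures assume binary covariates, a normal approximation, one step of selection and, for the ten-candidate figure, independence. The 268 events are those planned for the overall-effectiveness analysis; the mITT count may differ. The bias figures rest on assumed imbalances. Nothing here touches the primary analysis, and the SAP's correction for clustering is not in question.

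**What to change.** Replace the stepwise rule in section 3.6, item a, with one fixed list drawn from data the SAP already names: service area, village baseline diarrhoea admission rate and village size (both used to stratify the randomisation, section 2.2), and sex, SES quintile as categories and age band (section 3.3). Fit the model once and report it whatever the individual coefficients.

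Add one sentence saying how the village-level variance of Secondary Aim 1 is kept when child-level covariates are included, for example by standard errors clustered on village, and apply the same variance to the sex and SES interaction terms.

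The cost is SAP wording and a few degrees of freedom. With two age bands and linear village terms the list uses nine (1 + 1 + 1 + 1 + 4 + 1), eight more than the present model, some of them perhaps on covariates that prove weak. No new data are needed.

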### **4. INTERIM ANALYSIS**

There are no interim analyses for efficacy or effectiveness in this study. About 6 months before the end of data collection, an analysis of historical data that were compiled before the study start will be carried out to estimate the design effect for the primary outcome. It is possible that if the estimated design effect were much larger than the one assumed for sample size calculations, the study could be extended accordingly.

This analysis of historical data will not be used in the evaluation of study estimates of efficacy.

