## 2.5 Sample Size Considerations

### 2.5.1 Sample size calculations

The primary study endpoint will be admission for rotavirus gastroenteritis (see definitions, section 2.3.8). From 2003 to 2006 the average annual rotavirus admission rate to the Matlab Diarrhoeal Hospital among infants 0 to 11 months of age from the government comparison area was about 18.5 per 1000 and among infants 12 to 23 months of age it was 12.3 per 1000 (Table 3a); among infants 0 to 11 months of age from the intervention area it was 37.3 per 1000 and among infants 12 to 23 months of age it was 24.5 per 1000 (Table 3b). Because we will conduct surveillance among age-eligible infants continuously from study initiation, infants enrolled early will fall under longer surveillance while infants enrolled later will fall under brief surveillance (for example, only a few months). Additionally, because enrolment and surveillance for rotavirus diarrhoea will occur in the government comparison area and intervention area along different timelines, we used modeling to estimate a total study-period rotavirus diarrhoea hospitalization rate of 33 per 1000 infants (3.3%) (data not shown). With inclusion of infants admitted for rotavirus gastroenteritis at the Nayergaon and Kalirbazaar Community Treatment Centres, this rate may be slightly higher at 3.5%.

Because this is a cluster-randomized design, we must account for the intracluster (intra-village) correlation of acute rotavirus gastroenteritis. At the time of study planning, this value is not available for the study population. However, given the ubiquitous nature of rotavirus, we expected this value to be low (we assumed 0.02). Additionally, because we predefine clusters as villages for this study, we cannot set the cluster sizes to be equal; villages from the government comparison and intervention areas vary substantially in size (numbers of annual births). According to the timelines for enrolment for the 142 villages in from each area, the average cluster size is expected to be 65 with a coefficient of variation of cluster sizes is 0.96. Factoring in these values, along with the assumed intracluster correlation coefficient, into the calculation of the design effect for a cluster-randomized trial (Eldridge, 2006), we calculate a design effect of 3.48. Later estimations of the design effect based on rotavirus admission data for Matlab hospital place the design effect in the range of 2.9 to 4.5.

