We calculated sample size and power based upon a fixed number of events design and conditional on the total number of cases observed (Blackwelder, 1993; Chan 1998). The number of cases in each group was assumed to follow a Poisson distribution, with parameters  $\lambda_V$  for a vaccine villages and  $\lambda_U$  for the unvaccinated villages. Under this assumption, the number of vaccine cases,  $x_V$ , has a binomial distribution  $(X, P)$  conditional on  $X$ , the total number of cases, with  $P = \lambda_V / (\lambda_V + \lambda_U)$ . For the primary objective, we assumed 50% vaccine population (overall) effectiveness. With no design effect ( $DE=1$ ), observation of at least 77 admissions for rotavirus gastroenteritis among all age-eligible infants from vaccine and unvaccinated villages would ensure that the study has a minimum power of 80% to rule out a lower bound of 0% overall effectiveness. However, with a design effect of 3.48, a minimum of 268 admissions for rotavirus diarrhoea must be observed. Assuming a 3.5% total study-period attack rate in the unvaccinated villages, 268 admissions translates into an estimated minimum sample size of 10,210 infants (5105 in each group, vaccinated villages and unvaccinated villages) (Table 6).

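### Section 4's only stated condition for extending the study compares a historical design effect with 3.48; it leaves out the event count, and 3.48 does not match the planned village size

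*SAP*

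**What the plan says.** Section 4 rules out interim analyses of effectiveness. It plans that, about six months before data collection ends, "an analysis of historical data that were compiled before the study start will be carried out to estimate the design effect". It then adds that "if the estimated design effect were much larger than the one assumed for sample size calculations, the study could be extended accordingly". It gives no numerical threshold, no historical period and no event count.

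The assumed value comes from Section 2.5.1. There an ICC of 0.02 is assumed, "the average cluster size is expected to be 65 with a coefficient of variation of cluster sizes is 0.96", and "we calculate a design effect of 3.48". The same section reports that later estimates from Matlab hospital admissions "place the design effect in the range of 2.9 to 4.5".

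Sample size was calculated "based upon a fixed number of events design and conditional on the total number of cases observed": 77 admissions if there were no clustering, 268 at a DE of 3.48, and from these 10,210 infants. The paragraph after Table 6 expects about 11,650 infants. It warns that effectiveness below 50% or an attack rate below 3.5% would quickly cost power, and it responds by keeping enrolment and follow-up open to March 2011. Section 1 states that the SAP was finalised with "only a general idea of enrollment and total numbers of events".

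**The concern.** In an event-driven cluster design, the information is the number of events divided by the design effect. Section 4 watches the divisor and ignores the events. A low attack rate, which the SAP itself names as a risk, therefore cannot prompt an extension; the only response to it is a fixed end date. A large design effect, on the other hand, could prompt one even when admissions are plentiful.

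The yardstick is a second problem. By the SAP's own formula a design effect grows with village size, and 3.48 belongs to a smaller village than either the required or the expected enrolment implies. At stake is whether the study recognises, while it can still act, that it is short of information for the primary aim.

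**Working it through.** **Inputs (Sections 2.2 and 2.5.1, Table 6).** ICC 0.02; mean village size m = 65; CV of village size 0.96; 142 villages; 50% effectiveness, so that the vaccine villages' share of cases is P = 1/3 against 1/2 under no effect; 5% two-sided; attack rate 3.5% in unvaccinated villages; 1:1 allocation; 11,650 infants expected.

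**1. The SAP's figures reproduce.**
- DE = 1 + [(1 + CV²)m − 1] × ICC = 1 + (1.9216 × 65 − 1) × 0.02 = 3.48.
- Exact conditional binomial test, 0.025 per tail: power is 82.3% at 77 events and 78.1% at 76. From 77 upwards it stays at or above 80%.
- 77 × 3.48 = 268.
- With 50% effectiveness the average attack rate is 0.75 × 3.5%, so N = 268 / (0.035 × 0.75) = 10,210.

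The SAP's own criterion is therefore events / DE ≥ 77. Below, events / DE is called effective events. Exact power moves in a sawtooth, so it is given for the whole numbers on either side.

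**2. Too few events, DE as assumed.**
- 11,650 × 0.025 × 0.75 = 218 events, against 268 needed.
- 218 / 3.48 = 62.8 effective events; exact power is 69% at 62 and 75% at 63.
- Break-even attack rate at 11,650 infants: 268 / (11,650 × 0.75) = 3.07%, not far below the assumed 3.5%.

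The design effect equals the assumed one, so Section 4's condition is not met.

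**3. Large DE, ample events.** Take the top of the reported range, 4.5, and 400 events as an illustration. The requirement is 77 × 4.5 = 347. Effective events are 400 / 4.5 = 88.9; exact power is 86% at 89 (88% at 88). The DE is 29% above 3.48, yet no extension is needed.

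**4. The benchmark against the planned size.** ICC 0.02 and CV 0.96 are held fixed, and the attack rate is 3.5%.

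| Infants | Per village (÷ 142) | DE | Events | Events / DE | Events needed (77 × DE) |
|---|---|---|---|---|---|
| 9,230 | 65.0 | 3.48 | 242 | 69.7 | 268 |
| 10,210 | 71.9 | 3.74 | 268 | 71.6 | 288 |
| 11,650 | 82.0 | 4.13 | 306 | 74.0 | 318 |

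The value 3.48 goes with 142 × 65 = 9,230 infants, fewer than the 10,210 to which it is applied. At the required and the expected enrolment, effective events fall short of 77 by about 7% and 4%. Exact power there is about 76-81% (71 and 72 effective events) and 79-83% (73 and 74).

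**5. An extension moves the DE as well.** Suppose an extension adds infants to the same villages at the same attack rate and ICC. With DE held at 4.13, 318 / 306 suggests that 4% more infants would do. With DE recomputed, 20% more infants give 98.5 per village, DE 4.76, 367 events and 367 / 4.76 = 77.0. About 20% more is needed.

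**The case against.** The strongest reply has four parts.

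- **Section 4 is permissive.** It says what might be done, with no threshold, so there is no firm rule that can be shown to misfire. This stands. A reader might infer that a DE of 4.5 would set off an extension, but the SAP does not say whether 4.5 counts as large enough. The cases in steps 2 and 3 show what the condition leaves out, not what the sponsor would have done.
- **The SAP does respond to a low attack rate.** It expects 11,650 infants against 10,210 and keeps the study open almost to the end of the winter season. This also stands, so Section 4 is not the SAP's only protection of power. But that response is a fixed date and is not tied to observed admissions. Once DE is recomputed at 82 infants per village, the apparent margin over 10,210 no longer reaches 77.
- **The SAP does not say that the historical DE would be used unscaled.** A reader might infer that it would be compared with 3.48 as it stands, with the roughly twofold difference in admission rates between service areas left in. The text is silent on scaling, on adjustment for area and on the historical period, so this is an unaddressed risk and not a shown error. Nor do the documents support reading the 2.9 to 4.5 range as a product of how many years were pooled. That needs an assumed between-village variance and an assumed split of births, and other reasonable choices remove the match.
- **Inference is untouched.** The primary model in Section 3.5 estimates its scale parameter from the trial's own village data. This is correct: the point concerns power and the extension decision only.

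Fuller extension criteria may stand in the protocol, which was not available. That does not remove the mismatch between the condition written here and the sizing written here.

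**Conclusion.** The point holds in a limited form. The one condition for extension that this SAP states omits the quantity on which its sample size is built. A fall in the attack rate from 3.5% to 2.5% would take power to roughly 69-75% without engaging that condition. Separately, 3.48 is too low a benchmark for the planned trial: the SAP's inputs give 3.74 to 4.13, and 72 to 74 effective events in place of 77. That second shortfall is small in power terms.

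These sizes rest on 50% effectiveness, an ICC of 0.02 and a size CV of 0.96 that stay fixed as villages grow, and the attack rates shown. The 2.5% rate and the 400 events are illustrations, not forecasts. Using pre-study data is not a fault, and a check of pooled events blind to arm would not spend alpha either. The change is worth making before data collection ends, but it is not a threat to the validity of the primary analysis.

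**What to change.** Rewrite the extension paragraph of Section 4 so that it:

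1. names the historical period, and estimates the ICC or the between-village CV within service area, in line with the area term in the primary model;
2. recomputes the DE at the trial's own expected village sizes, and again at the extended sizes if an extension is considered;
3. bases the decision on pooled, arm-blind admissions projected to the end of the study, divided by that DE, compared with 77;
4. restates the power from that ratio if the study is not extended.

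Correct the benchmark in Section 2.5.1 to match the enrolment to which it is applied. The cost is a few lines of text and one short calculation from historical data and pooled counts, with no arm-level data. The stated power may come out slightly lower than the SAP now implies.
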